## **17. Study Discontinuation Criteria**

### **17.1 Patient Discontinuation**

Patients have the right to voluntarily withdraw from the study at any time for any reason. In addition, the investigator has the right to withdraw the patient from the study at any time. Reasons for withdrawal from the study may include, but are not limited to the following:

- Patient withdraws consent at any time

- Any medical condition determined by the investigator may endanger the patient's safety if he or she continues the study
- The investigator determines that it is in the best interests of the patient
- Patient noncompliance, specifically defined as unwillingness to participate in a 3-month assessment of neurological status and function

Every effort should be made to obtain information about patients who withdrew from the study. The main reasons for withdrawal from the study should be recorded on the corresponding CRF. Patients who withdraw from the study will not be replaced.

### **17.2 Study Treatment Discontinuation**

The treatment with the investigate medication should be terminated immediately if the patients experience any of the following:

- Any serious gastrointestinal bleeding.
- Uncontrollable hyperglycaemia (blood sugar >22.2 mmol/L)
- Anaphylactic reaction
- Continuation of the study drug would be detrimental to the patient's well-being.
- Withdrawal for personal reasons.

According to the intention to treat (ITT) principle, patients who discontinue study treatment prematurely will continue in the study and be followed up to the 90th day.

### **17.3 Study and Site Discontinuation**

The investigators has the right to terminate this study in any case of concern about the safety of patients caused by new information. The reasons for terminating the study may include, but are not limited to:

- The incidence or severity of adverse events in this or other studies indicates a potential health hazard to patients.
- Patient enrolment is unsatisfactory

The investigators have the right to close a site at any time. Reasons for closing a site may include, but are not limited to, the following:

- Excessively slow recruitment
- Poor protocol adherence
- Inaccurate or incomplete data recording
- Non-compliance with the International Conference on Harmonization guideline for Good Clinical Practice
- No study activity

## **18. Statistical Analysis**

This study will test whether treatment of patients with acute ischemic stroke with intravenous methylprednisolone will lead to a lower mRS score at 90 days.

### **18.1 Determination of sample size**

The current trial is designed detect a shift on the modified Rankin Scale score, which represents the global disability, to a lower score. The expected distribution of the modified Rankin Scale score, derived from the EVT for acute anterior circulation ischemic stroke (ACTUAL) registry and the Highly Effective Reperfusion evaluated in Multiple Endovascular Stroke Trials (HERMES) collaboration, is as follows: 7%, 20%, 16%, 11%, 13%, 8% and 25%.

The sample size was calculated using the cumulative proportion of patients with mRS 0-2. We assume a moderate effect of 7% absolute increase in the cumulative proportion of patients with mRS 0-2 in the intervention group, compared with controls, indicating an odds ratio (OR) of 1.33, which have substantially exceeds the minimal clinically important difference. In order to demonstrate the expected treatment effect with a type-1 error  $\alpha=0.05$  (two-tailed) and a power of 80% ( $\beta=20\%$ ). A sample size of  $n=1588$  patients ( $n=794$  per treatment group) is required.

The intention-to-treat principle will be applied to the primary analysis and, therefore, to safeguard against dilution of the treatment effect associated with an approximate 5% non-adherence rate (due to loss to follow-up, consent withdrawal and other reasons), we initially planned to enrol  $n=1672$  patients ( $n=836$  per treatment group) for this study. This estimation was performed based on PASS (NCSS, LLC, Kaysville, Utah, USA) version 15.0.

## **18.2 Analysis population**

### **18.2.1 Intention-to-Treat Population**

The ITT population includes all patients randomized into the trial who were recorded as receiving any amount of study drug, even if the subject does not receive the correct treatment, or does not follow the protocol until completion. The ITT population will be the primary analysis population for the efficacy endpoints and subjects will be analysed according to the treatment group to which they were assigned at randomization.

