| Statistical Methods | 
All efficacy analyses will be conducted on data from all randomly assigned patients according to the intention-to-treat principle. All efforts will be made to minimize the amount of missing data. Sensitivity analyses based on different hypotheses
                                                                                                                                                                                                                                                                                                                                                                                                                                                                                                                                                                                                                                                                                                                                                                                                                                                                                                             |

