#### **13.4.1 Methylprednisolone and its Placebo**

Patients will be assigned to receive either a placebo or methylprednisolone, with a dosage of 2mg/kg (based on estimated or actual weight if known, not exceeding a maximum dose of 160 mg) per day for a duration of 3 days. The initial study drug will be administered as soon as possible after randomisation. It is recommended that the initial study drug administrated before arterial access closure, but it should not be delayed more than 2 hours after arterial access closure. All patients will be treated according to the current Chinese Stroke Association guidelines for clinical management of cerebrovascular disorders. Risk factors such as diabetes mellitus, hypertension, hyperlipidaemia, hyperhomocysteinaemia, obesity, drinking and smoking should be managed appropriately.

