### **18.2.3. Safety Population**

The Safety Population includes all patients who received any amount of study drug. In case of violation of the randomization scheme, patients will be classified according to the treatment they actually received. Patients will be assigned to the different populations prior to unblinding of the database. Patients who withdraw informed consent immediately after randomization and are not to receive any treatment should be excluded from Safety Population.

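### Section 18.2.1 defines the primary ITT population as dosed patients only, which contradicts the synopsis; expected bias is small in this blinded trial, but the text must be reconciled

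*Supplement*

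**What the plan says.** All references are to protocol version 2.0.

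- Section 18.2.1: "The ITT population includes all patients randomized into the trial who were recorded as receiving any amount of study drug". Patients given the wrong treatment or not completing the protocol stay in, and everyone in the set is analysed by assigned arm. The section adds: "The ITT population will be the primary analysis population for the efficacy endpoints".
- Section 1, Synopsis, Statistical Methods: "All efficacy analyses will be conducted on data from all randomly assigned patients according to the intention-to-treat principle".
- Section 18.1: "The intention-to-treat principle will be applied to the primary analysis". This is given as the reason for a 5% increase in sample size.
- Section 18.2.3: "The Safety Population includes all patients who received any amount of study drug". It also foresees randomised patients who are never treated: "Patients who withdraw informed consent immediately after randomization and are not to receive any treatment should be excluded from Safety Population".
- Sections 13.4 and 13.4.1: a start within 15 minutes of randomisation is recommended, preferably before arterial access closure. The outer limit for the first dose is that "it should not be delayed more than 2 hours after arterial access closure".

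**The concern.** The synopsis set and the section 18.2.1 set differ by exactly the patients who were randomised and never dosed. Section 18.2.3 shows that the protocol expects such patients. Under 18.2.1 they leave the primary analysis because of something that happened after randomisation, yet the result would still be reported as intention-to-treat.

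Two things are at stake. First, an exclusion made after randomisation can break the balance that randomisation created, if those excluded differ between arms in number or prognosis. Second, where a protocol states two primary populations, the choice between them is open at analysis, and it could be made after results are known.

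**Working it through.** **1. Membership of the sets**

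| Set | Source | Who is in it | Arm used |
|---|---|---|---|
| Efficacy analyses | Synopsis | all randomised | ITT principle |
| ITT | 18.2.1 | randomised, any study drug recorded | as assigned |
| Safety | 18.2.3 | any study drug | as received |
| Per-protocol | 18.2.2 | subset of the ITT set | received the assigned treatment |

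The 18.2.1 and Safety sets hold the same patients and differ only in arm labelling. The clause in 18.2.1 on wrong or incomplete treatment does not bring back anyone who was never dosed. No population defined under Analysis population in section 18.2 contains all randomised patients; only the synopsis sentence provides for that.

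**2. The plan's own sample size**

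Inputs from section 18.1: the expected mRS distribution "is as follows: 7%, 20%, 16%, 11%, 13%, 8% and 25" per cent, so control mRS 0-2 = 7 + 20 + 16 = 43%; a 7-point gain, so 50%; two-sided alpha 0.05; power 80%.

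- n per arm (unpooled variance) = (1.960 + 0.842)² × (0.43×0.57 + 0.50×0.50) / 0.07² = 793.06, rounded up to 794, or 1588 in total. This matches the plan.
- 1588 / 0.95 = 1671.6, so 1672 (836 per arm). This matches too.

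**3. Possible bias from dropping undosed patients**

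Assume no treatment effect, 43% mRS 0-2 in both arms, a share u undosed in one arm and none in the other, and a rate q of mRS 0-2 among the undosed. The values of u and q are assumptions.

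- Bias = (0.43 − u·q)/(1 − u) − 0.43
- Standard error at 836 per arm = √(2 × 0.43 × 0.57 / 836) = 0.0242
- Type I error = 1 − Φ(1.96 − bias/SE) + Φ(−1.96 − bias/SE)

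| u in one arm | q | Bias (points) | Type I error |
|---|---|---|---|
| 1% | 0 | 0.4 | 5.4% |
| 1% | 20% | 0.2 | 5.1% |
| 2% | 0 | 0.9 | 6.5% |
| 2% | 20% | 0.5 | 5.4% |

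If the two arms lose the same share with the same prognosis, the bias is zero.

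**4. Power under each definition**

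Assume an equal undosed share u in both arms, a 7-point effect in dosed patients and none in undosed patients. Power uses the pooled-variance two-proportion formula. As written, n per arm is 836(1 − u) and the effect stays at 7 points. With everyone kept, n per arm is 836 and the effect is 7(1 − u) points.

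| u | n per arm, dosed only | Power, dosed only | Power, all randomised |
|---|---|---|---|
| 0% | 836 | 81.9% | 81.9% |
| 0.5% | 832 | 81.7% | 81.5% |
| 1% | 828 | 81.5% | 81.1% |
| 2% | 819 | 81.1% | 80.4% |
| 5% | 794 | 79.9% | 77.9% |

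These figures use the plan's dichotomised scale. The primary analysis is the ordinal shift. Under proportional odds with an odds ratio of 1.33, power at 1672 with no undosed patients is about 91%, so the real margin is wider.

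**The case against.** The strongest reply is blinding. Allocation is concealed, placebo is visually identical, and patients are assigned to populations before unblinding. A patient who never received a dose cannot have reacted to it, and staff cannot withhold an arm they cannot identify. Non-dosing may track prognosis, but to bias the comparison it must also differ by arm, and the documents offer no clear route for that. This stands. It is why the one-arm illustration is unlikely: if about 17 undosed patients (2% of 836) split at random, the chance that all fall in the same arm is 2 × 0.5¹⁷, about 1.5 in 100,000.

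Other core protections are also present. Patients are analysed as assigned, and those who stop treatment early are followed to day 90. Among possible causes of non-dosing, only consent withdrawal is documented, and those patients may have no 90-day mRS under either definition.

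A reader might infer more than the documents support:

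- That the primary analysis is certainly not ITT, or that nobody plans to analyse everyone randomised. The synopsis does plan it. The details are referred to SAP section 12.1, and the SAP is not among the documents shown.
- That the 84 extra patients (1672 − 1588) measure the undosed. Section 18.1 gives that allowance for loss to follow-up, consent withdrawal and other reasons together.
- That bias could reach 2.3 points, from 0.43/0.95 − 0.43. That needs about 42 undosed patients in one arm, none in the other and no good outcomes among them. Under a random split its probability is about 5 in 10¹³.

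None of this reconciles the two definitions. Both rules are in the protocol itself, so the conflict does not depend on the SAP.

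**Conclusion.** The inconsistency is real and stands in version 2.0: the set that section 18.2.1 calls ITT is a modified-ITT set, at odds with the synopsis and with section 18.1. Expected bias is small, and zero if exclusion is balanced in number and prognosis. The 0.9-point bias and 6.5% type I error mark an unlikely case, not an estimate. All the sizes rest on an assumed undosed share, because the documents give none. The reason to act is that the primary population must be single and correctly named before results are known. A dosed-only primary set can be defended in a blinded trial, but it has to be declared as such, and here the synopsis promises something else.

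**What to change.** In section 18.2.1, define the ITT population as all randomised patients, analysed in their assigned arm whether or not any study drug was given, to match the synopsis. Keep randomised-and-dosed as a sensitivity set labelled modified ITT. Report undosed patients by arm with reasons, and seek their 90-day mRS and vital status as far as consent allows. State in section 18.2.2 which set the per-protocol population is drawn from, since that section calls it a subset of ITT and later speaks of exclusions from the randomised patients. Any SAP definition should agree.

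The cost is the wording change and follow-up of the undosed patients. N stays at 1672. On the plan's dichotomised scale, dilution costs about 0.4 points of power at 1% undosed, 0.7 at 2% and 2.0 at 5%; only the last falls materially below the 80% target, at 77.9%.

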### **18.2.2. Per-Protocol Population**

The PP population is defined as the subset of the ITT population excluding major protocol violators deemed to have the potential to affect patient outcome in terms of efficacy.

The PP population includes patients who actually received the assigned treatment and do not have major protocol violations or deviations. Major protocol violations or deviations will be identified in a blinded fashion prior to database lock. More specifically, patients with anyone of the following criteria will be excluded from the PP population. These deviations will be determined based on the medical monitors' records, as well as programmatically, using the following criteria at a minimum:

- Received but did not complete treatment with study drug, or dose of study drug administered outside recommended dose.
- Received study drug after 2 hours after arterial access closure.
- Violated inclusion or exclusion criteria.

A list of patients to be excluded from the randomized patients to create the PP-Efficacy analysis will be established and validated by the Steering Committee prior to unblinding.

### **18.2.3. Safety Population**

The Safety Population includes all patients who received any amount of study drug. In case of violation of the randomization scheme, patients will be classified according to the treatment they actually received. Patients will be assigned to the different populations prior to unblinding of the database. Patients who withdraw informed consent immediately after randomization and are not to receive any treatment should be excluded from Safety Population.

## **18.2 Analysis of Efficacy—primary endpoint**

The primary efficacy analysis will estimate the effect of treatment with intravenous methylprednisolone and with the placebo in acute ischemic stroke patients.

The primary efficacy outcome is the global disability defined by mRS score at 90 days post-randomization. Adjusted common odds ratio or assumption free method will be calculated. The adjusted covariates include age, baseline NIHSS score, pre-stroke mRS, baseline ASPECTS score, use of intravenous thrombolysis, time from onset to randomization, and occlusion location. (Details are described in SAP Section 12.1). We will analyse the primary outcome in the intention-to-treat (ITT) and per-

protocol (PP) population.

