## **7. Organizational Structure**

## **7.1 Funding**

MARVEL trial is an investigator-initiated study which is organized by the second affiliated hospital of the Army Medical University and conducted in 82 centres in China. MARVEL will be funded by the National Natural Science Foundation of China. Methylprednisolone and its placebo are manufactured and provided by Chongqing Lummy Pharmaceutical Co., Ltd., Chongqing, China. The funder had no involvement in the study design, data collection, analysis and interpretation, writing or decision to submit the paper.

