## **11. Randomization**

Randomization will be done by a web-based APP (Jinlingshu) on mobile phone or computer (<https://jinlingshu.com/>). The automated system will assign an appropriate set of study medication to each patient. Eligible patients are randomized to treatment with either intravenous methylprednisolone or placebo with a ratio of 1:1.

Randomization will be stratified by participating centre with permutation block size of 4. Randomization will be completely concealed by having both web-based real-time allocation and identical appearance of methylprednisolone sodium succinate and placebo bottles. (All bottles will have a unique number. Subjects will be assigned a

random serial number according to the time they were enrolled, and corresponding masked medications will be provided).

The randomization list will be prepared by the independent statistical centre using SAS 9.4. It will only be sent to the data coordination centre responsible for central randomization and data management, the pharmacy centre responsible for treatment packaging.

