### **18.3 Analysis of Efficacy – secondary endpoints**

The mRS score will be used to evaluate the proportion of patients with a score = 0 to 4 *versus* 5 or 6, 0 to 3 *versus* 4 or higher, 0 to 2 *versus* 3 or higher, 0 to 1 (or return to pre stroke morbidity) *versus* 2 or higher and at day 90 $\pm$ 7. The adjusted risk ratio will be calculated by fitting the GLM models separately.

NIHSS score at 5-7 days or at early discharge and Functional health status quality of life 90 ( $\pm$ 7) days after randomization (EQ-5D-VAS). The EQ-5D-VAS will be compared between the methylprednisolone group and the placebo group via GLM.

Normality and variance homogeneity of residuals will be accessed graphically. The win ratio method will be used if normality assumption is seriously violated.

The significance of each test is determined at the two-sided alpha level of 0.05. The specific statistical model for analysing each of these outcome measures will be detailed in the Statistical Analysis Plan (SAP).

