### **18.6 Adjustment for Covariates and Subgroup Analyses**

In addition to the primary and secondary analyses adjusting for age, baseline NIHSS score, pre-stroke mRS, baseline ASPECTS score, the use of intravenous thrombolysis, time from onset to randomization, and occlusion location, exploratory analyses will be conducted to determine the potential roles of common baseline characteristics and assess potential heterogeneity of treatment effect across subgroups. The primary pre-specified subgroups as follows will be explored.

- age
- sex
- baseline NIHSS score
- pre-stroke mRS
- baseline ASPECTS score
- intravenous thrombolysis

- time from last known well to randomization. (mins)
- occlusion location
- Complete Reperfusion defined as Extended Thrombolysis in Cerebral Infarction grade 2c or 3
- Patients with any radiological haemorrhages
- Patients with symptomatic haemorrhages

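### Randomisation is stratified by centre, but the covariate list the protocol gives for the efficacy models leaves centre out; this is mildly conservative if centres differ and cheap to mend

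*Supplement*

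**What the plan says.** Section 11 of protocol version 2.0 sets the design: "Randomization will be stratified by participating centre with permutation block size of 4". The synopsis agrees, and no other stratification factor is named. Section 7.1 says the trial is "conducted in 82 centres in China"; the synopsis says about 80.

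For the primary outcome, section 18.2 (analysis of the primary endpoint) reads: "Adjusted common odds ratio or assumption free method will be calculated". It continues: "The adjusted covariates include age, baseline NIHSS score, pre-stroke mRS, baseline ASPECTS score", followed by use of intravenous thrombolysis, onset-to-randomisation time and site of occlusion. The synopsis lists the same seven variables. Section 18.6 ties them to the secondary outcomes as well: "In addition to the primary and secondary analyses adjusting for age, baseline NIHSS score", and so on through the same list. None of the three places has centre as a fixed effect, a random effect or a stratum, and no reason is given.

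Detail is deferred to the SAP. Section 18.2 points to SAP section 12.1 after the list, and section 18.3 says of the secondary outcomes: "The specific statistical model for analysing each of these outcome measures will be detailed in the Statistical Analysis Plan (SAP"). That SAP is not in the supplement. The safety analyses in section 18.4 name no covariates at all.

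**The concern.** Blocking within centre balances the arms inside each site, so differences between sites largely cancel from the treatment comparison. The true sampling spread of the estimate is therefore smaller than under unrestricted randomisation. A model without centre does not credit this: it leaves the between-centre variation in the error, so the nominal standard error is too large for the design and the test is conservative.

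At stake is precision that the stratification has already paid for, together with a clear match between design and analysis. Some variation between centres is plausible from the protocol itself. Gastrointestinal prophylaxis and glucose treatment follow local practice (section 13.4.2), and patients who decline video have their 90-day mRS determined by site neurologists (section 16.1.1).

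**Working it through.** **Inputs.** From the documents: 82 centres, blocks of 4, 1:1 allocation, control mRS distribution 7/20/16/11/13/8/25%, mRS 0-2 rising from 43% to 50%, odds ratio 1.33, two-sided alpha 0.05, 794 per arm (1588 in total), 5% inflation (sections 7.1, 9.3, 11, 18.1). Assumed: the ICC, varied from 0 to about 0.11.

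**1. The plan's own sample size.** With unpooled variance, n per arm = (1.960 + 0.842)² × (0.43×0.57 + 0.50×0.50) / 0.07² = 7.849 × 0.4951 / 0.0049 = 793.1, so 794. The pooled form gives 796. Inflation: 1588 / 0.95 = 1671.6, so 1672. The figures reproduce. They make no allowance for centre, so this point does not make them wrong. Average site size is 1588/82 = 19.4 to 1672/82 = 20.4 patients.

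**2. Binary approximation (mRS 0-2, 794 per arm).** With arms balanced within centre, true variance ≈ (1 − ICC) × nominal variance. Put f = √(1 − ICC). The nominal SE of the difference is √(2×0.465×0.535/794) = 0.0250, so 0.07/SE = 2.796.

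- SE too large by 1/f − 1
- True alpha = 2 × [1 − Φ(1.96/f)]
- Power without centre = Φ[(2.796 − 1.96)/f]
- Power with centre = Φ(2.796/f − 1.96)

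| ICC | SE too large by | True alpha | Power without centre | Power with centre | Difference (points) |
|---|---|---|---|---|---|
| 0 | 0% | 0.050 | 79.9% | 79.9% | 0 |
| 0.01 | 0.5% | 0.049 | 80.0% | 80.2% | 0.2 |
| 0.03 | 1.5% | 0.047 | 80.2% | 81.0% | 0.8 |
| 0.05 | 2.6% | 0.044 | 80.5% | 81.8% | 1.3 |
| 0.10 | 5.4% | 0.039 | 81.1% | 83.8% | 2.7 |

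The loss is relative to a centre-adjusted analysis. Power without centre does not fall as the ICC rises.

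**3. Ordinal analysis.** Whitehead's formula at odds ratio 1.33 and N = 1588: z = ln(1.33) × √[N(1 − Σp̄³)/12] = 0.285 × √(1588 × 0.968/12) = 3.23. Power = Φ(3.23 − 1.96), about 90%.

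Simulation: 82 unequal centres, blocks of 4, N = 1588, odds ratio 1.33, 1300 runs per setting. A proportional-odds model with treatment only is set against a van Elteren test stratified by centre.

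| Latent ICC | Power without centre | Power stratified | Mean log OR without centre |
|---|---|---|---|
| 0 | 88.8% | 88.3% | 0.283 |
| 0.015 | 89.5% | 88.3% | 0.279 |
| 0.03 | 88.1% | 88.1% | 0.279 |
| 0.06 | 86.8% | 88.2% | 0.274 |
| 0.11 | 86.7% | 89.3% | 0.267 |

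Monte Carlo error is about 0.9 points on power. There is no visible gain at 0.03 or less, and 1.4 and 2.6 points at 0.06 and 0.11. The 2.6 may be slightly generous, because the stratified test rejected 6.4% under the null in that setting. The mean log odds ratio falls by (0.283 − 0.267)/0.283 = 5.7%, from an odds ratio of about 1.33 to 1.31, while the model SE stays at 0.0886. So in a common-odds-ratio model part of the effect is shrinkage of the estimate. The SE is too large only relative to the true spread.

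**4. A second simulation.** A rank-based comparison with 82 centres of 20 and a true odds ratio of 1.27 gave gains of 0.4, 1.8 and 3.2 points at latent ICC 0.02, 0.05 and 0.10. The direction and size agree, but 1.27 is not the plan's odds ratio, so its absolute power levels (74% to 79%) say nothing about whether the planned power is met.

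**The case against.** The strongest reply is that the SAP is missing. Model detail is expressly left to it, section 18.2 says the covariates include the seven items, and a random effect or stratum for centre often appears only in a SAP. This stands as a limit: a reader might infer that the trial's final analysis ignores centre, and the documents do not show that. It does not remove the point. The covariate set was not left open, since the protocol states it three times, each time without the one factor that governs allocation.

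The second reply is size, and most of it stands. The documents give no ICC. At modest values the loss is within simulation noise. None of the calculations includes the seven covariates, which may absorb part of the variation between centres, so the real loss may be smaller than shown.

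Third, a random intercept changes the estimand to a centre-conditional odds ratio, and a centre-stratified assumption-free method may not readily carry seven covariates. Giving those up could cost more precision than centre returns. Both are fair and are taken into the fix.

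**Conclusion.** The point holds for the protocol text: the stated efficacy models omit the only stratification factor. The consequence is conditional and small. If outcome varies between centres beyond the seven covariates, the nominal SE is about 0.5% to 5.4% too large for ICCs from 0.01 to 0.10, and the common odds ratio shrinks slightly towards 1. The power forgone runs from negligible at 0.03 or less to about 1 to 3 points at 0.05 to 0.11. These figures rest on an assumed ICC and near-exact balance within centres.

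A reader might go further and infer that the trial is underpowered, that its p-values are unsafe, or that the safety models share the fault. None of this is supported. At odds ratio 1.33 power stays at about 80% or above in every setting. The error is on the conservative side. Section 18.4 gives no covariate list from which centre could be said to be missing. Severity is minor: a free or cheap improvement.

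**What to change.** In the synopsis and sections 18.2, 18.3 and 18.6, add centre as a random intercept beside the seven covariates, in the primary ordinal model and in the adjusted secondary efficacy models. Pre-specify, before unblinding, the rule for pooling very small sites. Do not use 81 fixed effects: at about 20 patients per site they could bias an ordinal model. If the assumption-free method is the one used, stratify it by centre and keep covariate adjustment as far as the method allows. Bring SAP section 12.1 into line. If the team prefers to leave centre out, it should say so and give the reason.

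Cost: a few sentences and a slightly more complex model, with no new data. The odds ratio becomes centre-conditional, and the report should say so.
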